### Phase 2: testing phase

2.3

In the second phase of the project, the developed algorithm from phase 1 will be tested in a newly recruited naturalistic cohort of 300 patients to assess, under real-world conditions, the ability of the algorithm to correctly discriminate patients according to treatment response. Moreover, in the context of the new recruitment, patients’ focus groups and surveys will be set to assess perspectives and needs about predictive tools in precision medicine.

#### Study participants and clinical assessment

2.3.1

A naturalistic cohort of 300 MDD patients is being recruited to assess, in real-world conditions, the capability of the algorithm to correctly predict the treatment outcomes. Patients are recruiting by the Department of Psychiatry at the University of Münster (Germany), by the Department of Medical Sciences and Public Health in Cagliari (Italy) and by the Department of Adult Psychiatry at Poznan (Poland). The broad inclusion criterion is a diagnosis of moderate to severe MDD and an age over 18 years. The exclusion criteria for Phase 2 are the following: (a) a lifetime history of schizophrenic, schizoaffective, or bipolar disorder; (b) personality disorder, drug abuse disorder, alcohol misuse and abuse disorder, OCD, PTSD as primary diagnosis; (c) comorbidity with alcohol and substance dependence; (d) severe neurological disorders (e.g., multiple sclerosis, Parkinson, dementia; intellectual disability; debilitating medical disorders). Diagnoses are confirmed according to the DSM-5 using the SCID-5-CV (clinical version) and the SCID-5-PD (personality disorders) diagnostic scale. At the baseline (T0), the Childhood Trauma Questionnaire (CTQ) is administered.

Patients are treated with antidepressant (AD) in monotherapy or with complex psychopharmacology such as two ADs or AD associated with other drugs (second-generation antipsychotics, mood stabilizers, lithium, FT3/FT4). Combination with diverse types of ongoing psychotherapy is accepted, if initiated prior to baseline.

Clinical assessment will be performed at 5 time points: baseline (T0), 2 (T1), 4 (T2), 8 (T3), and 12 (T4) weeks, using the MADRS, the Beck Depression Inventory II (BDI-II), the Beck Anxiety Inventory (BAI), the Columbia-Suicide Severity Rating Scale (C-SSRS) and the UKU Side Effects Rating Scale. At all time-points except the T1, the Functioning Assessment Short Test 24 items (FAST), the Quality of Life Questionnaire (SF-36) and the Perceived Stress Scale-10 (PSS-10) are administered. Moreover, at T0 and at T3 the Repeatable Battery for the Assessment of Neuropsychological Status (RBANS) are applied for the evaluation of cognitive symptoms in MDD patients.

This study involving human participants was reviewed and approved by the Ethics Committee “Ethik-Kommission Westfalen-Lippe” (Münster, Germany, registration number: 2021-103-f-S). Based on the German ethics approval, local ethics approval was obtained at the other clinical trial sites. The patients/participants provided their written informed consent to participate in this study. The study protocol was registered on ClinicalTrials.gov as NCT05537558.

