## Abstract

Major depressive disorder (MDD) is the most common psychiatric disease worldwide with a huge socio-economic impact. Pharmacotherapy represents the most common option among the first-line treatment choice; however, only about one third of patients respond to the first trial and about 30% are classified as treatment-resistant depression (TRD). TRD is associated with specific clinical features and genetic/gene expression signatures. To date, single sets of markers have shown limited power in response prediction. Here we describe the methodology of the PROMPT project that aims at the development of a precision medicine algorithm that would help early detection of non-responder patients, who might be more prone to later develop TRD. To address this, the project will be organized in 2 phases. Phase 1 will involve 300 patients with MDD already recruited, comprising 150 TRD and 150 responders, considered as extremes phenotypes of response. A deep clinical stratification will be performed for all patients; moreover, a genomic, transcriptomic and miRNomic profiling will be conducted. The data generated will be exploited to develop an innovative algorithm integrating clinical, omics and sex-related data, in order to predict treatment response and TRD development. In phase 2, a new naturalistic cohort of 300 MDD patients will be recruited to assess, under real-world conditions, the capability of the algorithm to correctly predict the treatment outcomes. Moreover, in this phase we will investigate shared decision making (SDM) in the context of pharmacogenetic testing and evaluate various needs and perspectives of different stakeholders toward the use of predictive tools for MDD treatment to foster active participation and patients’ empowerment. This project represents a proof-of-concept study. The obtained results will provide information about the feasibility and usefulness of the proposed approach, with the perspective of designing future clinical trials in which algorithms could be tested as a predictive tool to drive decision making by clinicians, enabling a better prevention and management of MDD resistance.

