#### Study participants and clinical assessment

2.2.1

Three hundred MDD patients were already recruited from one unit participating in PROMPT consortium (IRCCS Fatebenefratelli, Brescia, Italy): half were classified as TRD and the other 150 as responders. For all of them, diagnosis of moderate to severe MDD according to the DSM-IV was confirmed using the Italian version of the SCID-I diagnostic scale. The diagnosis of personality disorders was made on the basis of clinical symptoms evaluation in agreement with the DSM-IV. Exclusion criteria were the following: (a) a lifetime history of schizophrenic, schizoaffective, or bipolar disorder; (b) personality disorder, substance abuse, alcohol abuse or dependency, obsessive compulsive disorder (OCD), or post-traumatic stress disorder (PTSD) as the primary diagnosis; (c) comorbidity with an eating disorders; (d) comorbidity with alcohol and substance dependence; (e) intellectual disability and cognitive impairment; (f) neurological disorders (i.e., Parkinson’s disease, multiple sclerosis, Alzheimer’s and other dementias, epilepsy, strokes, brain tumors, traumatic conditions of the nervous system); (g) comorbidity with other severe medical illness and severe autoimmune diseases (i.e., cancers, Crohn’s Disease, Rheumatoid Arthritis (RA), Lupus, Scleroderma, Psoriasis, Myasthenia gravis, Sjögren syndrome, Systemic lupus erythematosus); (h) pregnancy.

On the basis of clinical evaluation, TRD was defined as a failure of treatment to produce response or remission for patients after two or more treatment attempts of adequate and recommended dose and duration. Based on clinical judgment by the treating psychiatrists, MDD patients were classified as responders when they achieved response or remission in terms of a reduction in symptomatology with the first antidepressant treatment attempt of adequate dose and duration. For all patients, detailed socio-demographic (such as, age, sex, working and marital status) and clinical information (such as, age of onset, severity, psychiatric and physical comorbidities) was collected. Symptom evaluations were made using Montgomery-Åsberg Depression Rating Scale (MADRS) at the presentation of the patients to psychiatric services or hospital, in concomitance with the blood collection.

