#### Development of the predictive algorithm

2.2.9

We will combine the multi-omic features identified to play a role in TR to generate a predictive model for TRD on Phase 1 data using state-of-the art statistical and machine learning methods for classification. We favor tree-based methods such as random forests or extreme gradient boosting over traditional regression models because they are not equipped to identify complex interacting risk structures empirically and have failed to model sex-specific associations (31). Standard methods of internal validation (e.g., bootstrap or cross-validation) will be used to estimate performance, to avoid over-fitting and to ensure reproducibility of the model. To select between models, we will use standard metrics such as Accuracy and F-measure on the validation set. Potential biases that may affect the inclusiveness of the models (e.g., sex or ethnicity issues) will be carefully considered.

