#### Data integration and testing of the algorithm and predictive accuracy

2.3.6

Phase 2 data will be used to externally validate the model. This new naturalistic cohort will be different in the nature of patients as well as their provenance. We will assess the performance of the model using different measures such as C-index, accuracy, true positive rate and false positive rate. We will compute these measures for the whole cohort as well as in stratified groups by sex, ethnicity, and country of origin to assess potential biases of the model.

We also want to address the challenge of designing algorithms and tools that are both usable and effective, which are the two main obstacles in the clinical application of advanced statistical and ML models based on multi-omics data. Interpretability, intended as the ability to appropriately explain the reasoning behind the predictions, will be considered as a mandatory component of the model and can be achieved by using intrinsically interpretable models like random forests, by evaluating the model structure and importantly the feature importance, for instance through model agnostic techniques such as SHAP (SHapley Additive exPlanations) (32).

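### Phase 2 validation should report performance by prior treatment failure, because a pooled AUROC can partly reflect resistance already present at baseline rather than early detection

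*Protocol article*

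**What the plan says.** **Aim.** The Abstract describes an algorithm that "would help early detection of non-responder patients, who might be more prone to later develop TRD". The patient of interest is one who is not yet resistant.

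**Training.** Section 2.2.9 will "generate a predictive model for TRD on Phase 1 data". In section 2.2.1, "TRD was defined as a failure of treatment to produce response or remission for patients after two or more treatment attempts", and the comparison group responded to its first adequate attempt.

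**Phase 2 entry.** Section 2.3.1 states: "The broad inclusion criterion is a diagnosis of moderate to severe MDD and an age over 18 years". The exclusions, (a) to (d), are psychiatric, neurological or medical conditions. None concerns the number of earlier treatments or existing resistance. On treatment, the same section says: "Patients are treated with antidepressant (AD) in monotherapy or with complex psychopharmacology such as two ADs or AD associated with other drugs"; the other drugs named are second-generation antipsychotics, mood stabilizers, lithium and thyroid hormones.

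**Evaluation.** Section 2.3.6 says: "We will compute these measures for the whole cohort as well as in stratified groups by sex, ethnicity, and country of origin". Treatment history is not among the named strata. The measures are introduced as examples and include the C-index, which equals the AUROC for a binary outcome.

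**Link between history and outcome.** The Introduction (section 1) states that the chance of success falls as more treatments fail.

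**The concern.** The model learns to separate patients with at least two failures from patients with none. If the Phase 2 cohort also contains patients with two or more failures, a score that only recognises established resistance, or the drug exposure that goes with it, will rank them high. By the article's own premise these patients also respond less often. The pooled AUROC then rises above the AUROC within each history group, and part of it repeats what a clinician learns by counting earlier failures.

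At stake is what the validation can support. The project is meant to inform future trials of the algorithm as a decision aid. A single pooled figure cannot show how far the algorithm predicts in patients who are not yet resistant, or whether the omics layers add anything to treatment history.

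**Working it through.** **1. The plan's own figure.** Section 2.3.4 gives AUROC A = 0.8, event proportion 0.3, 95% CI width 0.125 and N = 272. The Hanley-McNeil variance is

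Var = [A(1−A) + (n1−1)(Q1−A²) + (n0−1)(Q2−A²)] / (n1·n0), with Q1 = A/(2−A) = 0.6667 and Q2 = 2A²/(1+A) = 0.7111.

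With n1 = 0.3 × 272 = 81.6 and n0 = 0.7 × 272 = 190.4, SE = 0.03187 and the width is 2 × 1.96 × 0.03187 = 0.1249. The 272 reproduces and is not in dispute.

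**2. A flag that knows only the past.** Let q be the share with TRD at T0, a their week-8 non-response rate and b the rate in the rest. None of these is in the article; all are assumptions. For a binary flag marking existing TRD, with no information within either group:

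- event rate: P = qa + (1−q)b
- sensitivity: s = qa/P
- false positive rate: f = q(1−a)/(1−P)
- pooled AUROC = (1 + s − f)/2

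Central case, q = 0.30, a = 0.80, b = 0.50: P = 0.59, s = 0.24/0.59 = 0.407, f = 0.06/0.41 = 0.146, AUROC = 0.630.

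| q | a | b | pooled AUROC |
|---|---|---|---|
| 0.20 | 0.75 | 0.55 | 0.566 |
| 0.30 | 0.80 | 0.50 | 0.630 |
| 0.30 | 0.85 | 0.40 | 0.690 |
| 0.40 | 0.85 | 0.40 | 0.722 |
| 0.30 | 0.50 | 0.50 | 0.500 |

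The last row shows that the effect vanishes when history does not affect response.

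**3. A continuous score.** This second illustration uses normally distributed scores, q = 20% to 40%, non-response of 70% to 80% with TRD at T0 and 30% to 40% without, and a score that separates TRD from non-TRD with AUROC 0.8 to 0.9.

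| AUROC within each history group | pooled AUROC |
|---|---|
| 0.50 | 0.56 to 0.69 |
| 0.60 | 0.65 to 0.76 |
| 0.65 | 0.69 to 0.79 |

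**4. Precision in the non-resistant stratum.** With 300 recruited, and A = 0.8 and event proportion 0.3 kept as in section 2.3.4:

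| q | patients left | 95% CI width | recruits needed for 0.125: 272/(1−q) |
|---|---|---|---|
| 20% | 240 | 0.133 | 340 |
| 30% | 210 | 0.142 | 389 |
| 40% | 180 | 0.154 | 454 |

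The width depends on the event proportion: 210 patients give 0.120 at a proportion of 0.5, against 0.142 at the plan's 0.3.

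**The case against.** The strongest reply is that a broad cohort is a declared and legitimate choice. Section 2.3 sets the Phase 2 task as discriminating patients by treatment response under real-world conditions. Section 2.3.6 says openly that these patients will differ in nature from those of Phase 1, and the Abstract names prediction of treatment response as well as of TRD. Predicting week-8 response in previously treated patients is a fair part of that. Further analyses may also stand in a fuller plan that is not shown. This stands, and it is why the whole-cohort analysis should be kept. It does not remove the gap between a pooled figure and the early-detection aim.

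A reader might also infer three stronger things that the article does not support:

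- **That resistant patients are known to be enrolled in number.** No share is given. Combination or augmentation can be given without two failed adequate attempts, so the treatment sentence alone proves nothing about resistance. The point rests on that sentence read with the entry and exclusion lists.
- **That the study could declare success on past resistance alone.** The article sets no success threshold and calls itself proof-of-concept. Within the ranges used above, a flag with no other information stays below the planning value of 0.8. Even at 0.722 with 300 patients and 58% events, the 95% CI is about 0.67 to 0.78.
- **That existing TRD would be counted as the event, giving an AUROC of 1.0.** Sections 2.3 and 2.3.3 make treatment response the target. The TRD wording in section 2.3.4 is a separate matter to reconcile.

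**Conclusion.** The point holds as a cheap improvement to the validation analysis. It is not a fault in recruitment or in the sample size calculation. The direction follows from the article's own premises, provided that patients already resistant at T0 are present, score higher and respond less. The size is unknown because their share is not stated. The illustrative 0.57 to 0.72 (0.63 centrally) rests on assumed shares of 20% to 40% and on assumed non-response of 75% to 85% against 40% to 55%. Restricting the main analysis to non-resistant patients would be a trade-off against the naturalistic target and the planned precision, and the point does not require it.

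**What to change.** Keep the whole-cohort analysis. Record the number of failed adequate attempts at T0, if this is not already collected, and add two items to section 2.3.6:

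1. The AUROC with its 95% CI, separately for patients with fewer than two and with two or more prior failures. State that the former is the evidence for early detection.
2. A benchmark model using only prior failures and baseline clinical variables, and the paired AUROC difference between it and the integrated algorithm in the same patients (DeLong or bootstrap).

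The cost is one history item, some wording, and lower precision in the non-resistant stratum. If 20% to 40% of 300 patients are already resistant, the 95% CI width there is about 0.133 to 0.154 at the plan's AUROC and event proportion, instead of 0.125. For a stratified analysis added to the whole-cohort one, that loss is acceptable without more recruitment.

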#### Biospecimens

2.3.2

Fasting blood samples are collected at T0, T2, T3, and T4 in each clinical recruitment center, which perform the first pre-processing steps. One EDTA Tube for DNA extraction and PAXGene Blood RNA Tube collected at T0 are sent to the same unit (IRCCS Fatebenefratelli, Brescia, Italy) that performed the DNA and RNA extractions for phase 1 to have uniform laboratory standards and reduce biases using the same methods described above in phase 1. The omics profiling (genomic, pharmacogenetic, transcriptomic, miRNomic) are carried out in the same sites and with the same methods described in phase 1. All remaining samples of unused biospecimens [EDTA tube, PAXGene Blood RNA, plasma, serum collected at each time point as well as peripheral blood mononuclear cell (PBMC)] (collected at T0 and T3) are stored locally at the recruitment sites and at the end of the project will be sent to Coordinator site in Münster, where the PROMPT Consortium biobank will be established using Centraxx standards.

#### Outcomes

2.3.3

Our study has three major outcomes. The primary outcome is symptom improvement at week 8, as measured by the percent change in the MADRS score from baseline. Secondary outcomes include response and remission rates at 4, 8, and 12 weeks according to the MADRS. Tertiary outcomes include: (1) changes in scores of self-reported depressive symptoms at 2, 4, 8, and 12 weeks compared with baseline, as measured by the BDI; (2) response and remission rate at 4, 8, and 12 weeks according to BDI-II; (3) changes in scores of anxiety symptoms at 2, 4, 8, and 12 weeks compared with baseline, as measured by the BAI; (4) changes in scores of suicidal risk at 2, 4, 8 and 12 weeks compared with baseline, as measured by the C-SSRS; (5) changes in scores of perceived stress at 4, 8 and 12 weeks compared with baseline, as measured by the PSS-10; (6) changes in scores of psychosocial functioning at 4, 8 and 12 weeks compared with baseline, as measured by the FAST and Quality of Life Questionnaire (SF-36); (7) changes in scores of cognitive symptoms at 8 weeks compared with baseline, as measured by the RBANS; (8) and side effects at 4, 8, and 12 weeks, as assessed by the UKU Side Effect Rating Scale.

The response is defined as a ≥ 50% decrease in the assessment of interest (MADRS, BDI-II) at weeks 4, 8, and 12 compared with the baseline. Remission is defined as a score of ≤9 for MADRS and ≤ 9 for BDI-II. Moreover, the response to treatment is also computed at each time point considering different thresholds of symptom reduction (>20, >50, and > 80%) on the MADRS total score, as well as on the BDI-II total score. This approach allows defining fast responders (>20% after 2 weeks), partial responders (>50%) and full responders (>80%) after 8 weeks as compared to non-responders (<50% change in MADRS score) at week 8.

#### Sample size calculations

2.3.4

Considering an Area Under Receiver Operating Characteristic (AUROC) Curve of 0.8, given a proportion of 0.3 of TRD, a confidence interval width of 0.125 at 0.95 confidence level, we computed that a sample size of at least 272 MDD patients will be enough to validate the predictive algorithm developed in the phase 1 of the PROMPT project.

#### Data management

2.3.5

The data management process is the responsibility of the project coordinator. Clinical and biological data collection, analysis, storage, security, and sharing are consistent with the standard operating procedures that ensure patient pseudonymization.

Several data sets are generated, stored and shared during the project, including clinical data and omics data (genomic, transcriptomic, miRNomic, methylomic, and metabolomic).

We use data and metadata standard for file names and directories, clinical data and omics data. Access to data is restricted to qualified members of the project team. During the project, each data set is locally stored (secure servers, controlled access and backup copies). Secure protocols for data transfer such as sftp in concordance with national and European GDPR regulations are being used. For after the project, raw omics data and associated clinical metadata will be anonymized and hosted at the European Genome-Phenome Archive (EGA), following the MINSEQE standards. Codes and scripts will be deposited in software repositories (e.g., GitHub).

#### Data integration and testing of the algorithm and predictive accuracy

2.3.6

Phase 2 data will be used to externally validate the model. This new naturalistic cohort will be different in the nature of patients as well as their provenance. We will assess the performance of the model using different measures such as C-index, accuracy, true positive rate and false positive rate. We will compute these measures for the whole cohort as well as in stratified groups by sex, ethnicity, and country of origin to assess potential biases of the model.

We also want to address the challenge of designing algorithms and tools that are both usable and effective, which are the two main obstacles in the clinical application of advanced statistical and ML models based on multi-omics data. Interpretability, intended as the ability to appropriately explain the reasoning behind the predictions, will be considered as a mandatory component of the model and can be achieved by using intrinsically interpretable models like random forests, by evaluating the model structure and importantly the feature importance, for instance through model agnostic techniques such as SHAP (SHapley Additive exPlanations) (32).

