Several clinical variables are associated with an unfavorable treatment outcome in MDD, such as earlier disease onset, greater severity, presence of psychiatric comorbidity, suicidal behaviors, and early life adversity (6). From a biological perspective, TRD is associated with specific molecular underpinnings, which are only partly known. Concerning transcriptomics, there is evidence of distinct patterns of gene expression, both in the central nervous system and in peripheral tissues, such as blood (7). Moreover, expression alterations of both coding genes and microRNAs (small non-coding RNAs that regulate gene expression) have been related to the lack of response to antidepressant treatment (8). In addition, several studies also indicated the existence of a genetic vulnerability to non-response to antidepressant drugs and TRD (7, 9). In animal models, RNA-seq on different brain regions after antidepressant treatments showed largely distinct gene changes associated with treatment response (10). Moreover, accumulating evidence shows that transcriptional changes seen across several brain regions in animal models of depression coincide with genetic risk factors in depressed human patients. This indicates the likelihood that peripheral changes in gene expression might reflect to some extent some aspects of brain function (11).

In this context, the identification of predictive markers will help the early detection of non-responder patients, who may be more prone to later develop TRD. However, the use of single sets of markers (either clinical or molecular) have shown limited predictive power and low replicability, indicating that the etiology of MDD in non-responder patients remains to be better understood. Through multi-omics integration, machine learning methods have the potential to model the interactions between several molecular layers (such as DNA or RNA) to predict a clinical endpoint using a holistic model (12). It is conceivable that the integration of diverse sets of predictors might increase the accuracy in the identification of non-responder and TRD patients.

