The overall objective of the PROMPT (“Toward PrecisiOn Medicine for the Prediction of Treatment response in major depressive disorder through stratification of combined clinical and -omics signatures”) consortium, which is funded by the European ERA PerMed funding scheme, is to apply an integrated precision medicine approach in MDD through the combination of clinical, genomic, transcriptomic and sex-related data. The core objective is to create a new algorithm for the prediction of treatment response, which could be tested and validated in future clinical trials. This algorithm might represent a new tool for clinicians to drive decision-making, based not only on patients’ clinical features, but also on their genetic and transcriptomic background. An additional objective is to evaluate the potential use of a predictive pharmacogenetic tool in clinical practice from different perspectives and needs of various stakeholders involved in MDD treatment. Moreover, it is important to stress that the development of such an innovative precision medicine tool is central, but only part of the process to advance MDD treatment. Considering the later clinical application is crucial, and shared decision making (SDM) is increasingly viewed as the gold standard in patient-healthcare professional communication (13). SDM is a patient-centered approach that aids empowerment by supporting patients to actively take part in developing an informed decision about further treatment jointly with healthcare professionals based on clinical options as well as a patient’s individual preferences (14–16). Although SDM has been reported to lead to better decisions, increased patient participation, patient satisfaction, and treatment adherence and avoidance of overtreatment, its application in the mental health field is still rare (16, 17). Furthermore, multiple factors have been reported to influence SDM. This includes personal characteristics of the engaging parties, such as sex, age, clinical knowledge, years of experience, spoken language, or the level of education, factors relating to the interaction process, such as providing information or establishing a trustful relationship, and factors concerning broader structures of the healthcare system, for example, time constraints (18). In PROMPT, we consider application and SDM from the beginning and seek to identify factors that might come into play when patients and healthcare professionals come together to decide specifically about using the developed algorithm in clinical practice.

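### Phase 2 is described and sized for one integrated model, so the planned analyses do not estimate the added value of integration, although the design would allow it

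*Protocol article*

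**What the plan says.** **Rationale.** The Introduction of the protocol article states that "the use of single sets of markers (either clinical or molecular) have shown limited predictive power and low replicability", and then: "It is conceivable that the integration of diverse sets of predictors might increase the accuracy in the identification of non-responder and TRD patients". It describes the intended tool as drawing on genetic and transcriptomic background in addition to clinical features. The Abstract adds that "The obtained results will provide information about the feasibility and usefulness of the proposed approach".

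**Objective.** The Introduction says "The core objective is to create a new algorithm for the prediction of treatment response". It states no objective of showing superiority over single marker sets, and the Abstract calls the project a proof of concept.

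**Phase 1 model choice (section 2.2.9).** The multi-omic features found in Phase 1 are combined into a predictive model. "To select between models, we will use standard metrics such as Accuracy and F-measure on the validation set". The candidates are not described as including clinical-only or single-layer models.

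**Phase 2 validation (section 2.3.6).** "Phase 2 data will be used to externally validate the model". The measures are absolute: "We will assess the performance of the model using different measures such as C-index, accuracy, true positive rate and false positive rate". They are repeated "in stratified groups by sex, ethnicity, and country of origin to assess potential biases of the model", that is, by patient group and not by predictor layer.

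**Phase 2 size (section 2.3.4).** At least 272 patients, from an AUROC of 0.8, a TRD proportion of 0.3 and a 95% CI of width 0.125. Planned recruitment is 300.

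**The concern.** The rationale is comparative (integration against single sets), but the stated test is absolute (how well one model discriminates). If the integrated model reached the AUROC of 0.80 that the plan anticipates, nothing in the described analyses would show how much of that came from omics. The Introduction itself lists clinical variables linked to poor outcome: early onset, severity, comorbidity, suicidal behaviour and early adversity. Such variables could supply part of the discrimination.

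What is at stake is the conclusion on usefulness. The tool requires genotyping, RNA sequencing and small-RNA sequencing. Whether that is worthwhile depends on what it adds to clinical data that are available anyway, and the plan as described gives no estimate of this.

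**Working it through.** **1. What the 272 measures.** The inputs from section 2.3.4 are A = 0.8, p = 0.3, full CI width 0.125 and 95% confidence. The Hanley-McNeil formula is

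SE² = [A(1−A) + (n1−1)(Q1−A²) + (n2−1)(Q2−A²)] / (n1·n2), with Q1 = A/(2−A) = 0.6667 and Q2 = 2A²/(1+A) = 0.7111.

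At N = 272, n1 = 0.3 × 272 = 81.6 and n2 = 190.4:

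- Numerator: 0.16 + 80.6 × 0.02667 + 189.4 × 0.07111 = 15.78
- Denominator: 81.6 × 190.4 = 15,537
- SE = √(15.78/15,537) = 0.0319
- Width = 2 × 1.96 × SE = 0.1249

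The smallest N with width at most 0.125 is 272, exactly the stated figure. At N = 300 the width is 0.1189. Two other variance formulas give 231 (Newcombe) and 306 (Obuchowski). The 272 is thus a precision calculation for one AUROC, with no comparison in it.

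**2. Whether anything else in the plan estimates the gain.** Section 2.3.6 mentions feature importance and SHAP. These apportion predictions within one fitted model. They do not say what external AUROC a model without the omics layers would have reached.

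**3. Whether the design allows a comparison.** Sections 2.3.1 and 2.3.2 provide for clinical data and all omics layers in Phase 2, with the Phase 1 laboratory methods. Reduced models trained in Phase 1 could therefore be scored on the same Phase 2 patients.

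**4. How precise a paired comparison would be.** The documents give no correlation r between the two AUROC estimates, so r is an assumption and is shown as a range.

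*N = 272, both models given the SE at AUROC 0.80.* SE(diff) = 0.0319 × √(2(1−r)).

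| Assumed r | SE(diff) | 95% CI half-width | Power for a true gain of 0.05 |
|---|---|---|---|
| 0.6 | 0.0285 | 0.056 | Φ(0.05/0.0285 − 1.96) ≈ 42% |
| 0.8 | 0.0202 | 0.040 | Φ(0.05/0.0202 − 1.96) ≈ 70% |

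*N = 300, integrated AUROC 0.80, r from 0.3 to 0.7.* SE(diff) = √(SE1² + SE0² − 2r·SE1·SE0). The gain needed for 80% power is (1.96 + 0.84) × SE(diff). The comparator AUROC is assumed.

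| Comparator AUROC | SE(diff) | Half-width | Power (two-sided 5%) | Gain for 80% power |
|---|---|---|---|---|
| 0.65 | 0.0394 to 0.0261 | 0.077 to 0.051 | 97% to >99% | 0.110 to 0.073 |
| 0.70 | 0.0386 to 0.0254 | 0.076 to 0.050 | 74% to 98% | 0.108 to 0.071 |
| 0.75 | 0.0374 to 0.0246 | 0.073 to 0.048 | 27% to 53% | 0.105 to 0.069 |

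With 272 patients and a comparator AUROC of 0.75, power over the same range of r is 25% to 49%.

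**The case against.** **A condensed article may omit comparators.** A full protocol or analysis plan might name benchmark models, and nothing in the article excludes them. This has weight, but the article does not leave Phase 2 validation open. It states the target, the types of measure, the strata and the basis of the sample size, and all of them concern one model. The point is a mismatch between the stated hypothesis and the stated test.

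**Superiority is not a declared objective.** This stands. The gain from integration is put forward only as conceivable, the core objective is to create the algorithm, and the study is a proof of concept. It limits the point to what may be claimed at the end. It does not remove it, because the Abstract promises information on usefulness.

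**Stronger readings that the documents do not support.**

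- A reader might infer that the integration question cannot be answered in this study. It can: the data to be collected allow the comparison, and only the described analyses leave it out.
- A reader might infer that the planned cohort could show or exclude a gain of 0.05. At r = 0.6 the half-width of 0.056 exceeds 0.05, so an observed gain of that size would have an interval including zero.
- Section 2.2.1 defines the Phase 1 groups by different treatment histories, and a reader might infer that DNA-only and clinical-only benchmarks would separate treatment-history signal in RNA from predictive signal. They would not by themselves, because a gain or its absence fits either explanation.
- A reader might infer that the comparison uses data already in hand. Section 2.3.1 describes Phase 2 recruitment as ongoing.

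**Conclusion.** The point holds as a mismatch between rationale and analysis. Phase 2 as described estimates how well one integrated model performs and gives no estimate of what integration adds. It should be corrected, because the remedy is cheap and any conclusion about the value of the omics layers depends on it.

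A paired comparison would be informative for gains of about 0.10 and weak for gains of about 0.05, so a null difference would not exclude a small gain. This rests on the plan's own AUROC and prevalence, the Hanley-McNeil variance, and assumed correlations and comparator AUROCs. The 42% to 70% range also gives the comparator the SE that belongs to an AUROC of 0.80.

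**What to change.** 1. In Phase 1, train and lock by the same pipeline a clinical-only model, a DNA-only model and the integrated model. Restrict the clinical-only model to variables available in both phases. The article names the childhood trauma and suicidality instruments only for Phase 2, and its Phase 1 list is illustrative, so availability must be checked first.
2. In Phase 2, score all locked models on the same patients and report each AUROC.
3. Prespecify the paired AUROC difference, integrated minus clinical-only, with a 95% CI (for example by DeLong's method) as a key secondary estimate. Read it as an estimate and not as a pass-or-fail test.
4. Base any claim of added value from integration on that difference. If the comparison is not made, make no such claim.

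The cost is extra model fits. No additional patients are needed to report the estimate, but its precision stays as shown above. The downside for the sponsor is that the result may show little gain from omics.
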